### Concealment mechanism {16b}

Concealment will be ensured as the CleanWEB® platform will not release the randomization code until the patient has been recruited into the trial.

### Implementation {16c}

The allocation sequence is configured by the data manager who is blinded to the allocation group. Participants will be enrolled and assigned to interventions by investigators of the center team (different from the psychiatrist performing the clinical examination).

### Assignment of interventions: blinding

#### Who will be blinded {17a}

Participants will be informed of the group which they are allocated to. Care providers are informed of which treatment group they are facilitating. The psychiatrist performing the clinical examination and assessing the outcomes (at V0, V1, V2) is not involved in the randomization process and remains blind to the groups to which patients are attributed throughout the trial. The allocation sequence is configured by our data manager who is blinded to the allocation group.

In the Strasbourg center only, the clinical psychologist administrating the semi-structured interview will be blinded to the experimental arm of the patient (i.e., a clinical psychologist not involved in the trial to make sure that they had no previous contact with the participant).

### Procedure for unblinding if needed {17b}

The design is open-label with only outcome assessors and the clinical psychologist performing the semi-structured interviews being blinded so unblinding will not occur.

### Data collection and management

#### Plans for assessment and collection of outcomes {18a}

Self-report questionnaires will be completed on a survey software (Limesurvey) using a tablet computer at V0, V1, and V2, in order to increase the ease of use for participants.

Clinician-reported data will be collected on the online survey software (CleanWeb) by the investigators and will be stored on a secure hospital server.

The assessors will be trained to use the study instruments prior to the inclusion phase. The respective measurement tools that will be applied are described in the outcomes section {12} including information on reliability and validity. In order to promote data quality, we only included validated scales.

### Plans to promote participant retention and complete follow-up {18b}

Patients enrolled in the study will receive a compensation (i.e., 100 euros) at the end of the last visit with the psychiatrist. To receive the compensation, participants must have completed the visits V1, V2, and V3.

For patients in the three arms, in case of premature termination of participation in the study by decision of the investigator or the patient/guardian, the self-report questionnaires including the ISMI will be administered one last time to the exiting participant, if the patient/guardian agrees. A semi-structured evaluation interview will also be conducted. For patients who quit the study prematurely, all data collected before the decision to interrupt the study will be analyzed.

A participant starting psychotherapy in parallel to their participation in the protocol will be kept in the group for ethical and clinical reasons. Their data will be excluded from the study.

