### Criteria for discontinuing or modifying allocated interventions {11b}

Participants may withdraw their consent and request to leave the study at any time for whatever reason. The investigator must document the reasons for early discontinuation as fully as possible. The investigator has the right to discontinue a subject’s participation in the study, temporarily or permanently, for any reason that is in the best interest of the subject.

Participants who prematurely discontinue the study procedure will continue follow-up in the study until the end-of-study visit scheduled in the protocol. The criteria for premature termination of participation by the investigator are long-term hospitalization (more than 1 month).

For patients in the three arms, in case of premature termination of participation in the study by decision of the investigator or the patient/guardian, the self-report questionnaires including the ISMI will be administered one last time to the exiting participant, if the patient/guardian agrees. A semi-structured evaluation interview will also be conducted.

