### Sample size {14}

Taking the effects obtained in the article *Effects of a group psychoeducation program on self-stigma, empowerment and perceived discrimination of persons with schizophrenia* [72], for the TAU and ESS groups and adding a CFT group with a stronger and lasting effect, the means and standard deviations of the ISMI before the therapy, after the therapy, and after 6 months follow-up used to estimate the sample size are respectively 2.46 ± 0.39, 2.43 ± 0.29, and 2.46 ± 0.39 for the TAU group; 2.45 ± 0.48, 2.20 ± 0.41, and 2.40 ± 0.48 for the psychoeducation group; and 2.45 ± 0.48, 2.10 ± 0.41, and 2.20 ± 0.48 for the CFT group. With 84 patients in each group, the power is more than 85% between the TAU and psychoeducation groups after the therapy and more than 99% between CFT and the other groups after 6 months. In order to consider the possible loss to follow-up, the sample size is increased by 33% to obtain 112 patients in each group. The total sample size is therefore 336 participants.

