### Methods in analysis to handle protocol non-adherence and any statistical methods to handle missing data {20c}

Subjects with at least one non-missing data, for a given analysis, will be included in the analysis.

In order to minimize attrition bias, an intention-to-treat analysis and specific techniques for handling missing data will be performed.

Missing data frequency will be listed for every variable. A univariate and bivariate (i.e., for each relevant group) description will be provided. Monotone patterns will be looked for and a probable missing data mechanism (completely at random, at random, or not at random) will be identified.

Missing data will be treated according to their frequency in a given analysis. Simple deletion will be considered if the proportion of missing data is smaller than 3%. For a missing data proportion between 3 and 20%, multiple imputations will be used. For larger proportions of missing data, the relevance of each analysis will be discussed and, if required, specific models will be used.

Multiple imputations will be implemented and run directly within the Bayesian model scripts.

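### The exit ISMI is collected after the decision to leave, but the sentence on analysing leavers' data covers only what came before that decision

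*Protocol article*

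**What the plan says.** Only the protocol article is at hand. Four of its sections bear on the point.

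- **Discontinuation {11b} and retention {18b}.** Both provide an exit assessment in all three arms, "in case of premature termination of participation in the study by decision of the investigator or the patient/guardian". In that case "the self-report questionnaires including the ISMI will be administered one last time to the exiting participant, if the patient/guardian agrees".
- **Retention {18b}, same paragraph.** The analysis rule for leavers follows: "For patients who quit the study prematurely, all data collected before the decision to interrupt the study will be analyzed".
- **Discontinuation {11b}.** People who stop the study procedure are treated differently: "Participants who prematurely discontinue the study procedure will continue follow-up in the study until the end-of-study visit scheduled in the protocol".
- **Missing data {20c}.** The aim is stated as "In order to minimize attrition bias, an intention-to-treat analysis and specific techniques for handling missing data will be performed". The inclusion rule is "Subjects with at least one non-missing data, for a given analysis, will be included in the analysis". Multiple imputation is prescribed when 3 to 20% of data are missing. Above that, "For larger proportions of missing data, the relevance of each analysis will be discussed and, if required, specific models will be used".

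The ISMI is scheduled at V0, V1 and V2 only, and its fall from V0 to V1 is the primary outcome.

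**The concern.** The decision to end participation triggers the exit assessment, so the exit score necessarily comes after the decision. A cut-off placed at the decision therefore leaves out the measurement that the same paragraph arranges to collect.

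Someone who leaves the study before V1 has only a V0 score on the permitted side of the cut-off. Any model must then fill in that person's V1 value from baseline and from the course of those who stayed. The article itself gives reason to doubt that this is safe. Its introduction reports high drop-out from ESS in previous trials and attributes it to persisting shame, and lower drop-out is one aim of the CFT adaptation. If leavers do worse than their baseline predicts, and leave more often in one arm than in another, the comparison of arms is biased. A dated post-baseline score on these people is the information best placed to reduce that bias, and the sentence as written does not admit it.

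**Working it through.** **1. Order of events.** Decision to end participation, then exit ISMI (if agreed), then analysis of the data from before the decision. On that order, the ISMI scores each group has are:

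| Who | ISMI before the decision | ISMI after it | What is at stake |
|---|---|---|---|
| Leaves the study before V1 | V0 | exit score, if agreed | primary endpoint |
| Leaves the study between V1 and V2 | V0, V1 | exit score, if agreed | 6-month maintenance objective |
| Stops the study procedure but stays in the study | follow-up continues to the end-of-study visit | not applicable | nothing here |

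Only the first two rows are affected, and only the first touches the primary endpoint.

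**2. Against the missing-data section.** A leaver before V1 already has one non-missing value (V0), so the inclusion rule keeps the person in the analysis. What the retention sentence leaves out is that person's exit value. Someone included under intention-to-treat would then be represented by less outcome data than was collected.

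**3. Ceiling on the number affected.** The Sample size section says "In order to consider the possible loss to follow-up, the sample size is increased by 33" per cent. Reproducing its figures:

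- 84 × 1.33 = 111.7, rounded to 112 per arm; 3 × 112 = 336. This agrees with the stated total.
- Implied loss: 112 − 84 = 28 per arm, and 28/112 = 25%. Over three arms, 3 × 28 = 84 people.

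The allowance is not split by visit or by type of loss. A count of 28 per arm would be reached only if every loss were a formal exit before V1 with an agreed exit questionnaire. People who simply stop attending may give no exit score. If all of the 25% were missing at V1, it would pass the 20% limit, above which no missing-data method is fixed.

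**4. What bias would require (illustration; the gaps and the unequal loss rates are assumed).** Let p be the share of an arm lost before V1, and g the amount by which leavers' true V1 ISMI exceeds the value filled in for them. The arm mean is then too low by p × g. The ESS minus CFT difference, planned as 2.20 − 2.10 = 0.10, is understated by p(ESS) × g(ESS) − p(CFT) × g(CFT).

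| Assumed loss, ESS / CFT | Assumed gap, ESS / CFT | Shift in the contrast |
|---|---|---|
| 25% / 25% | 0.2 / 0.2 | 0.05 − 0.05 = 0 |
| 25% / 25% | 0.3 / 0.3 | 0.075 − 0.075 = 0 |
| 25% / 25% | 0.3 / 0.2 | 0.075 − 0.05 = 0.025 |
| 30% / 20% | 0.2 / 0.2 | 0.06 − 0.04 = 0.02 |
| 30% / 20% | 0.3 / 0.3 | 0.09 − 0.06 = 0.03 |

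Each shift is the whole bias under its assumptions. Using the exit score would recover some unknown part of it.

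**The case against.** The sentence does not say that later data are excluded. It stands in a section on retention, directly after the instruction to collect the exit questionnaires, and can be read as an assurance that leavers' data are kept. The missing-data section leans the same way. This stands, and it limits the point: a reader might infer that the plan discards the exit ISMI, but the document never says so. It does not rescue the wording, however. On the generous reading, nothing in the article says that the exit score is analysed. On the literal reading, an analysis that used it would go beyond the data named.

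A reader might also infer that the exit score is the only post-baseline ISMI on every early leaver. That is not so. Those who leave after V1 keep their V1 score, and those who stop only the study procedure stay in follow-up.

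Assigning an unscheduled score to a visit is commonly left to the full protocol or the SAP, so its absence from the article is not part of this finding. It appears below only because the corrected sentence needs it in order to be safe.

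Finally, the sample-size section applies one allowance to all arms. With equal loss and an equal gap, the bias in the contrast is zero. That also stands.

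**Conclusion.** The point holds as a fault in a stated rule. Read literally, the cut-off leaves out a post-baseline primary-outcome score that the plan chooses to collect, and this works against the plan's own aim of limiting attrition bias. The conclusion rests on the wording and the order of events, not on a calculation.

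Its size cannot be fixed from the document. The number of affected scores lies somewhere from none up to 28 per arm. A reader might take 84 scores, or a shift of 20 to 30% of the planned 0.10 (0.02 to 0.03), as the expected effect. Neither is supported: the first is a ceiling, and the second depends wholly on the assumed gap and the assumed 30%/20% split. What can be said is that the article's rationale makes loss that differs by arm plausible, and that the present wording leaves out information that would help if it occurs.

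**What to change.** In the retention section {18b}, replace the cut-off with: *all data collected up to and including the exit assessment will be analysed*. Align {11b} and {20c} with it, and record the date of the exit assessment.

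Use the exit ISMI as the V1 or V2 value only if its date falls in that visit's window. Otherwise do not relabel it, because a score taken early in therapy is not an end-of-treatment outcome. Enter it with its date as a post-baseline auxiliary variable in whichever missing-data model the plan leads to: the multiple imputation within the Bayesian model at 3 to 20% missing, or the specific models mentioned for larger proportions.

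The cost is an amended sentence, a recorded date and one extra variable in the model. No visit or questionnaire is added. The limits are that the score exists only for those who agree and is taken at varying times, so it can reduce bias from informative drop-out but cannot be relied on to remove it.

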### Data management {19}

All study data will be anonymized and then entered into an electronic case report form by the investigator or a person appointed by the investigator. A record of all changes made to the case report forms will be retained. This record must make it possible to ascertain for any given change the previous value, the date of the change, and the person who made the change. In accordance with ICH-GCP part 11, the investigator will append his or her signature to validate the authenticity and accuracy of the data in the case report form and the signature being electronic in electronic case report forms.

The database connected to the CleanWEB® electronic case report forms is hosted by TELEMEDICINE Technologies S.A.S., which possesses a number of dedicated virtual data centers. This company ensures data confidentiality, security, and integrity in accordance with a safety plan predefined by the sponsor and compliant with international recommendations (ICH-GCP part 11).

Trial data will be managed using the CleanWEB® software solution marketed by TELEMEDICINE Technologies S.A.S.

The list of people authorized to access the data is established by the project lead (coordinating/principal investigator) and the sponsor. Each person will be given strictly private, confidential login details to access the CleanWEB® input masks.

The coherence of the data collected will be verified by computer according to rules predefined between the sponsor and investigator and described in the monitoring plan. Queries will be sent to the investigator to clarify or correct certain data items. Every change will be traced via an audit trail, which may be consulted using CleanWEB®.

### Confidentiality {27}

The principal investigator will ensure that patient anonymity is observed and retains a confidential list identifying the patients included. In accordance with Article R.5121-13 of the French Public Health Code, the investigators and all those who are to work on the trial are bound by professional secrecy with regard in particular to participants and the results obtained. Without the sponsor’s consent, they may give information relating to the trials to the health minister, public health physicians, public health pharmacists, or the director and inspectors of the French National Agency for Medicines and Health Products Safety only.

The processing of personal data used within the framework of the study will be carried out according to the conditions laid down by Law 78-17 of January 6, 1978 (as amended) relating to information technologies, data files and civil liberties, and the regulations established to implement it, and by the European Directive UE 2016/679 dated 27 April 2016 related to personal data protection.

The data processing performed within the framework of this study will be carried out in accordance with all the provisions of reference methodology MR-001 on data processing in clinical trials as updated on 3r May 2018, by decision 2018-153 of the CNIL. Strasbourg University Hospital signed an MR-001 compliance statement on January 8, 2009.

### Plans for collection, laboratory evaluation, and storage of biological specimens for genetic or molecular analysis in this trial/future use {33}

N/A: no collection, laboratory evaluation, and storage of any biological specimens for genetic or molecular analysis in this trial/future use.

## Statistical methods

### Statistical methods for primary and secondary outcomes {20a}

The statistical analysis will have descriptive and inferential. The analyses will be carried out according to Bayesian methods.

The descriptive statistical analysis of the categorical variables will be performed by giving the frequencies, the cumulative frequencies, the proportions, and the cumulative proportions of each value. Whenever useful, cross-tabulations will be given with frequencies, proportions by row, proportions by column, and proportions of the total for each box in the table. For each continuous variable, the location parameters (mean, median, minimum, maximum, first and third quartiles) and the dispersion parameters (variance, standard deviation, range, interquartile range) will be given. The continuous variables will be described with histograms (with different bin width and with kernel density estimation). The normality of the distributions will be tested using a normality test, such as the Shapiro-Wilk test, and will be assessed graphically using a normal quantile plot.

To fulfill the primary objective, a generalized Bayesian linear regression model will be performed in order to estimate the effect of the treatment considering the center and the subject as a random effect. According to the distribution of the primary endpoint, i.e., the ISMI, the linear regression will be Gaussian, beta, or gamma.

To fulfill the secondary objectives, a generalized Bayesian linear regressions model will be performed: binary variables will be analyzed with a Bayesian logistic regression, score variables will be analyzed with a Bayesian beta regression, count variables will be analyzed with a Bayesian Poisson regression, and continuous variables will be analyzed with a Bayesian linear regression.

Priors will be firstly weakly informative and secondly more informative in a sensitivity analysis.

For each analysis, the posterior distribution of the parameter of interest (rate, proportion, mean, odds-ratio, regression coefficient, etc.) will be estimated using Markov chain Monte Carlo (MCMC) draws. The default number of iterations is 100,000 with a burn-in of 10,000 and a thinning of 2 on each of 3 chains. Algorithm convergence will be assessed graphically and with the Gelman-Brooks-Rubin (GBR) test. Autocorrelation will be assessed graphically, and if required, the number of iterations and thinning will be increased to reduce as much as possible the autocorrelation.

The mechanisms underlying the relationship between the intervention and the primary endpoint will be identified by carrying out an estimation of the causal mediation effect using the Baron and Kenny procedure though the quasi-Bayesian approximation. This allows for obtaining total, direct, indirect effects and the percentage of mediation. The potential mediators that will be tested include self-compassion, shame, and emotional dysregulation.

The statistical analyses will be run with the following software: R (with all the relevant packages), OpenBUGS, and JAGS, in their most up-to-date version at the time of analysis.

There is no significance level in Bayesian statistics. An effect will then be considered significant if its probability to exceed a prespecified threshold value, given the data, is strictly larger than 0.975 or strictly lower than 0.025. Credibility intervals will be provided at 95%.

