**Methods:**

This seven-center trial will involve 336 participants diagnosed with a severe mental illness and/or autism spectrum disorder and reporting high levels of self-stigma. Participants will be randomized into one of three treatment arms: 12 week-treatment of compassion-focused therapy (experimental arm), 12 week-treatment of Psychoeducation (active control arm), and TAU (treatment as usual—passive control arm). The primary outcome is the decrease of self-stigma scores on a self-report scale, i.e., ISMI, at 12 weeks. Secondary endpoints include sustainability of self-stigma scores (ISMI) and self-reported scores regarding target psychological dimensions, e.g., shame and emotional regulation, social functioning, and psychiatric symptoms. Assessments are scheduled at pretreatment, post-treatment (at 12 weeks), and at 6-month follow-up. Acceptability will be evaluated via (i) the Credibility and Expectancy Questionnaire at T0, (ii) the Consumer Satisfaction Questionnaire for Psychotherapeutic Services posttreatment and at 6-month follow-up, (iii) attendance, and (iv) dropout rates.

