#### Objectives {7}

The primary objective of our study is to evaluate the efficacy of a 12-week CFT group in decreasing self-stigma associated with severe psychiatric disorders and ASD by comparing its immediate effects to the effects of the Ending Self-Stigma (ESS) psychoeducation program [29] and to TAU.

The secondary objectives of our study are as follows:1. To evaluate the maintenance of effects on self-stigma scores in the three groups of treatment (CFT, ESS, and TAU) at 6-month follow-up (V2)2. To assess the effects of treatment (CFT, ESS, and TAU) at baseline (V0), post-treatment (V1), and at 6 months follow-up (V2) on target psychological dimensions (shame, self-compassion, emotional regulation, automatic avoidance tendencies toward mental illness)3. To assess the effects of treatment (CFT, ESS, and TAU) at baseline (V0), post-treatment (V1), and at 6 months follow-up (V2), on social functioning and psychiatric measures (psychiatric symptoms, depression, anxiety and stress, social functioning, access to care, recovery, functional remission)4. To assess the psychological factors mediating (shame, self-compassion, and emotional dysregulation) the efficacy of CFT on the self-stigma measure (V1)5. To evaluate the acceptability of the active interventions (CFT and ESS): pretreatment (V0) via a treatment credibility measure, during treatment via attrition rate, session attendance and group cohesion, and post-treatment (V1) via patient satisfaction and treatment side effects In addition, in the coordinating center, qualitative interviews will assess the acceptability of the active interventions.

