### Outcomes {12}

#### Primary outcomes

The decrease in scores on the Internalized Stigma of Mental Illness Scale (ISMI) [31] will be our primary outcome. The ISMI scale has good psychometric qualities in its various language versions [20]. This measure is a 29-item self-report questionnaire with five subscales: (1) alienation, (2) endorsement of perceived stereotypes, (3) discrimination, (4) social withdrawal, and (5) resistance to stigma. The participant must select their response on a 4-point Likert scale ranging from strongly disagree (1) to strongly agree (4).

The ISMI scale will be administered before therapy (V0), at the end of therapy (V1), and 6 months after the end of therapy (V2). If CFT is efficacious in reducing self-stigma, ISMI scores will decrease significantly between V0 and V1, and this decrease will be greater for CFT than for psychoeducation (ESS) and TAU.

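### The primary model, as worded, names no term that yields the primary contrast, the between-arm difference in the V0-to-V1 ISMI decrease

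*Protocol article*

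**What the plan says.** The primary question is a comparison of changes. The abstract's Methods paragraph has "The primary outcome is the decrease of self-stigma scores on a self-report scale, i.e., ISMI, at 12 weeks". The Primary outcomes section expects that "ISMI scores will decrease significantly between V0 and V1, and this decrease will be greater for CFT than for psychoeducation (ESS) and TAU". ISMI is collected at V0, V1 and V2. Objectives {7} makes the immediate effect primary and maintenance at the six-month visit the first secondary objective.

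The primary model is given in two sentences of Statistical methods {20a}. A generalized Bayesian linear regression is to be fitted "in order to estimate the effect of the treatment considering the center and the subject as a random effect", and "According to the distribution of the primary endpoint, i.e., the ISMI, the linear regression will be Gaussian, beta, or gamma". These name the response, the parameter of interest, the random effects and the candidate families. They do not say which visits enter or list the fixed effects. The missing-data section {20c} adds the general rule "Subjects with at least one non-missing data, for a given analysis, will be included in the analysis".

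**The concern.** A larger V0-to-V1 decrease in one arm is a treatment-by-visit contrast. Because randomisation makes the expected V0 difference zero, it can also be estimated as the V1 difference adjusted for V0. A single treatment coefficient in a model of raw ISMI is neither of these once several visits are pooled. It is the arm difference averaged over whichever visits are in the response.

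If V0 is among those visits, a null difference is averaged in and the effect is diluted. If V2 is among them, the 12-week result partly reflects the six-month effect, which the protocol treats as secondary. CFT versus ESS has most to lose: its planned V1 difference is only 0.10, and it is the comparison with the active control.

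**Working it through.** **Which data layouts fit the stated features?**

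- One V1 score per person: in the Gaussian model the subject random effect cannot be separated from the residual.
- One change score per person: the same difficulty, and beta and gamma regression cannot take a change that is zero or negative as it stands.
- V0 and V1 stacked: the subject effect is identified, but a lone treatment term averages in V0.
- V0, V1 and V2 stacked: identified, but the term averages all three visits.
- V1 and V2 stacked: identified, with V0 out of the response, but a lone treatment term averages the 12-week and six-month effects. For CFT minus ESS that is (-0.10 - 0.20)/2 = -0.15. Using V0 as a covariate here would itself be an unstated term.

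None of these gives the V0-to-V1 contrast without a term that the text does not name.

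**Inputs.** Sample size {14} gives mean ± SD at V0, V1 and V2: "2.46 ± 0.39, 2.43 ± 0.29, and 2.46 ± 0.39 for the TAU group"; 2.45 ± 0.48, 2.20 ± 0.41, 2.40 ± 0.48 for ESS; 2.45 ± 0.48, 2.10 ± 0.41, 2.20 ± 0.48 for CFT; 84 per arm. Assumptions: within-person correlation r = 0.5 to 0.7 (the article gives none), the 0.975/0.025 posterior rule treated as a two-sided 5% test of zero, and no allowance for therapy-group clustering.

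**The plan's own figure.** ESS versus TAU at V1: SE = √((0.29² + 0.41²)/84) = 0.0548, and power = Φ(0.23/0.0548 - 1.96) = 98.7%. The stated figure of more than 85% is met. No power is stated for CFT versus ESS at V1; the same formula with SDs of 0.41 gives 35%. The six-month power statement is a separate matter and does not affect this point.

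**What each parameter targets** (negative favours the first arm):

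| Contrast | V0-to-V1 change | V1 only | V0+V1 average | V0+V1+V2 average |
|---|---|---|---|---|
| CFT - ESS | -0.10 | -0.10 | -0.05 | -0.10 |
| CFT - TAU | -0.32 | -0.33 | -0.17 | -0.20 |
| ESS - TAU | -0.22 | -0.23 | -0.12 | -0.10 |

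For example, the CFT - ESS differences at the three visits are 0, -0.10 and -0.20. Their mean is -0.05 over two visits and -0.10 over three.

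**Power, CFT versus ESS.** Power = Φ(|difference|/√(2·variance/84) - 1.96). At r = 0.5:

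- V0+V1 average: variance = (0.48² + 0.41² + 2·0.5·0.48·0.41)/4 = 0.1488; SE 0.0595; Φ(0.05/0.0595 - 1.96) = 13%.
- Change: variance = 0.48² + 0.41² - 2·0.5·0.48·0.41 = 0.2017; SE 0.0693; Φ(0.10/0.0693 - 1.96) = 30%.
- V1 adjusted for V0: variance = 0.41²·(1 - 0.5²) = 0.1261; SE 0.0548; Φ(0.10/0.0548 - 1.96) = 45%.

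| Analysis | r = 0.5 | r = 0.7 |
|---|---|---|
| V0+V1 average | 13% | 12% |
| V0+V1+V2 average | 41% | 35% |
| V0-to-V1 change | 30% | 46% |
| V1 adjusted for V0 | 45% | 60% |

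On the V0+V1 average, CFT versus TAU has 89% and 85% power (change: above 99%), and ESS versus TAU has 62% and 57% (change: 94% and 99%).

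**Check by fitting.** In one simulated data set (4,000 per arm, r = 0.5), a treatment-only random-intercept model gave CFT - ESS of -0.045 on V0+V1 and -0.099 on all three visits. The arm-by-visit coefficient on V0+V1 was -0.088. The expected values are -0.05, -0.10 and -0.10.

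**The V2 leak.** Suppose there is no V1 difference and the V2 difference is -0.20, the plan's own CFT - ESS figure at six months. The three-visit average is then -0.20/3 = -0.067. At r = 0.5 its SE is 0.0576 and power is Φ(0.067/0.0576 - 1.96) = 21%; at r = 0.7 it is 18%. The nominal rate for a null 12-week effect is 5%. This scenario is illustrative, since the plan assumes a V1 difference of -0.10.

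**The case against.** The strongest reply is that the article never says treatment is the only fixed effect. It states a purpose and the random effects, and a condensed article may leave the model formula to the full protocol or analysis plan. The primary objective and hypothesis are clear elsewhere, so the treatment effect can be read as the V0-to-V1 contrast. A statistician who includes a subject effect would probably include time as well.

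Much of this stands. A reader might infer that the trial will test an average over visits that includes V0. The documents do not support that: no sentence excludes visit or baseline terms, the visits are not named, and a response of V1 and V2 with V0 as covariate also fits a subject random effect. The rule in {20c} covers every analysis and does not settle the layout. A reader might also infer that the estimate is halved whichever visits are used, but with all three visits CFT versus ESS is not diluted under the planning means. The power loss depends on the comparator as well. Against the change contrast it is about 17 to 34 points (30% less 13%; 46% less 12%); it is larger only against the baseline-adjusted analysis.

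What does not stand is that nothing more than detail is missing. The features that are stated do not combine into the stated contrast under any layout unless an arm-by-visit term or baseline ISMI is added.

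**Conclusion.** The point holds as a mismatch between the worded primary model and the primary hypothesis, not as proof that a wrong analysis will be run. Followed literally on V0 and V1, the model targets about half of each V0-to-V1 contrast (50% to 55%) and leaves CFT versus ESS with about 12-13% power, against 30-46% for change and 45-60% for baseline-adjusted V1. On all three visits CFT versus ESS keeps its size but no longer answers a 12-week question.

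The differences follow directly from the planning means. The power figures rest on r between 0.5 and 0.7, 84 per arm, and the posterior rule behaving like a two-sided 5% test. If a full analysis plan already contains the missing terms, the published text need only be brought into line with it.

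**What to change.** State in {20a} that the primary parameters are the arm differences in ISMI at V1, CFT versus ESS and CFT versus TAU. Estimate them in one of two ways:

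- regress V1 ISMI on arm and V0 ISMI, with centre as a random effect; or
- fit a repeated-measures model with visit and arm-by-visit terms, V0 as a covariate or with a common V0 mean across arms, and centre and subject random effects.

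A visit main effect alone is not enough, because the treatment coefficient would still be a visit average. Reserve the V2 contrast for the first secondary objective. A plain arm-by-visit contrast would also answer the hypothesis, but the two forms above make better use of the V0 score.

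The cost is a sentence of wording and a few model terms. V0 ISMI is already collected, so no new data or patients are needed.
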